### Secondary Outcomes

Parent-reported secondary outcomes include quality of life, parent mental health, service receipt, and treatment acceptability. Quality of life is measured with the EQ-5D-5L ([36]), completed by the parent both for themselves and on behalf of their child. Parent mental health is measured with the Depression and Anxiety Stress Scale—Short Form [37]. Parents will also complete the Client Services Receipt Inventory [38] to report their use of mental health, community rehabilitation, neuropsychology, and educational psychology services. The Client Services Receipt Inventory also includes questions assessing the financial burden of mental health concerns (ie, cost of transportation to and from appointments, medications, alternative childcare, missed work, etc) Finally, for families randomized to I-InTERACT-North, parents will complete a Parent Acceptability Questionnaire at the end of treatment to report their understanding of the structure and purpose of the treatment.

### Sample Size and Power Analysis

Based on the size of the research registries available for recruitment and pilot estimates of consent rate (70%), we anticipate that 382 families will consent to participate in the RCT. Using pilot estimates of adherence rate (86%), we anticipate that 328, 282, and 244 families will complete the 3-month, 6-month, and 12-month follow-up measurements, respectively. Samples of 122 participants in each condition at 12 months postbaseline will provide >95% power to detect an effect size of 0.64, which is a medium to large effect size conservatively based on our pilot data. This sample size also achieves a power of 95% for subgroup analyses with subgroups with a split of 50%, which is consistent with or close to that of our pilot data.

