**Methods:**

Families will be randomized (1:1) to either receive treatment or continue with care as usual for 12 months. Randomization will be stratified by child’s sex assigned at birth and baseline parent-reported child behavior intensity. Primary outcomes include positive parenting skills and child behavior at baseline, 3 months, 6 months, and 12 months. Secondary outcomes include parental mental health, quality of life, service usage, and feasibility including program reach and adherence. A sample size of 244 families will provide >95% power to detect an effect size of *d*=0.64. Based on attrition data from pilot studies, a target of 382 families will be enrolled. Parent reports of acceptability, adoption, and suggested adaptability of the program will be examined using cross-case thematic analyses. Primary efficacy analysis will be conducted using an intent-to-treat approach. Generalized estimating equations will be used to examine changes in positive parenting. Child behavior, quality of life, and parent mental health will be tested with repeated-measures analyses. Additional sensitivity and replication analyses will also be carried out.

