In response to these identified needs, our team at The Hospital for Sick Children developed the I-InTERACT-North program with and for families of children with CHD by adapting components from the parenting program I-InTERACT (Internet-based Interacting Together Everyday Recovery from Traumatic Brain Injury [25]). I-InTERACT was developed at the Cincinnati Children’s Hospital Medical Centre by Wade and colleagues [25] and uses in vivo coaching to improve positive parenting skills in a telehealth format. The original I-InTERACT program was shown to improve positive parenting skills and child behavior following pediatric traumatic brain injury (TBI [25,26]). While children with CHD share some underlying vulnerabilities with children with TBI, parents of children with CHD have reflected how their prenatal and neonatal experiences were unique from parents of children with TBI within an initial needs assessment [14]. Specifically, parents described stress beginning prior to or at birth, followed by significant fears and uncertainty during their child’s early medical and developmental journey. With this input, the I-InTERACT-North program caters specifically to families of children with congenital and neonatal conditions, including CHD, by providing new information regarding the unique neurodevelopmental and psychosocial impact of these conditions [27]. Likewise, program strategies are tailored to family-specific behavioral concerns, including psychoeducation, coaching, and problem-solving, to address their individual child’s needs in the context of their medical and treatment history. Following an initial pilot, which found I-InTERACT-North to be feasible, acceptable, and effective in increasing positive parenting skills and decreasing child behavior problems [28], our group further adapted the program to a novel stepped-care model, as informed by patient-orientated approaches, in which families can access needs-matched incremental supports (ie, an introduction session, an abbreviated program, and a full program [29]). Pilot data from the stepped-care program has demonstrated high acceptability, with strong parent-reported accessibility and adaptability of care to their family’s needs. Likewise, pilot data demonstrated the program’s success in improving positive parenting skills (*P*<.001; η^2^=0.850) and child behavior problems (*P*=.001; *d*=0.390). Without sacrificing efficacy, stepped-care I-InTERACT-North delivery also improves efficiency and contributes to precision mental health by offering scalable services that are adaptable to the needs of families.

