## Methods

### Study Design

The proposed hybrid type 1 study is a single-site, 2-arm, single-blind RCT designed to simultaneously assess (1) feasibility and acceptability of an RCT of stepped-care web-based parent support (ie, adherence, fidelity, costs, and acceptability) and (2) efficacy of the stepped-care I-InTERACT-North program in improving positive parenting skills and child behavior among families of children with CHD.

Hypothesis 1: based on our pilot data, we hypothesize that the stepped-care program will demonstrate program feasibility (ie, adherence and fidelity, >70%) and high acceptability (ie, based on postintervention program ratings, thematic analysis of feedback, >90%) across CHD families.

Hypothesis 2: we hypothesize that positive parenting skills and child behavior will improve at the end of the treatment among participants in the treatment arm compared to CAU and remain improved compared with CAU at 12 months. We consider positive parenting skills as the primary proximal outcome and child behavior (co–primary outcome) as mediated by improvements in parenting. We also consider secondary outcome changes in parent mental health and family quality of life.

After completion of baseline measures, families will be randomized to receive CAU or active I-InTERACT-North stepped-care treatment. Randomization will be stratified by sex assigned at birth (male, female) and baseline child behavior severity (Eyberg Child Behavior Inventory [ECBI] intensity *t* score above or below cutoff of 60) and executed by a computerized randomization system on REDCap (Research Electronic Data Capture; Vanderbilt University) [30]. Families in both conditions will complete follow-up measures at 3 months, 6 months, and 12 months postbaseline (Figure 1). Families randomized to CAU will receive no direct parent treatment other than clinical care provided in cardiac follow-up (ie, child assessment and consultation), which will be documented accordingly. The CAU families will be offered I-InTERACT-North after completion of their 12-month follow-up measurements. Participants cannot be blinded to their condition, but they will be blinded to primary outcomes and hypotheses. Independent study staff responsible for coding the primary outcomes (ie, positive parenting skills) will be blind to participant allocation, outcomes, and baseline or follow-up status.

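### The single >95% power claim at a 'conservative' d=0.64 does not cover the child-behavior co-primary (pilot d=0.390, about 86%), and the 95% subgroup power is not that of the planned moderator tests

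*Protocol article*

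**What the plan says.** The sample-size section of the Protocol article gives one main power statement. With 122 families per arm at the 12-month visit, the sample "will provide >95% power to detect an effect size of 0.64, which is a medium to large effect size conservatively based on our pilot data". The abstract repeats it: "A sample size of 244 families will provide >95% power to detect an effect size of *d*=0.64". Neither place says which outcome the effect size belongs to, and no significance level is given.

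The trial has two primary efficacy outcomes. Study Design names positive parenting as the primary proximal outcome and adds "child behavior (co–primary outcome"); Primary Outcomes and Primary Efficacy Analysis also treat child behavior, measured by the ECBI, as primary.

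The Introduction quotes stepped-care pilot effects for both: eta-squared 0.850 for positive parenting and, for the other, "child behavior problems (*P*=.001; *d*=0.390").

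On subgroups, the sample-size section adds: "This sample size also achieves a power of 95% for subgroup analyses with subgroups with a split of 50"%. Primary Efficacy Analysis then plans to refit the parenting model with sex, baseline behavior intensity and intervention step as moderators of the treatment effect, and to include interactions with these terms in the child-behavior model.

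**The concern.** One effect size serves two co-primary outcomes whose quoted pilot effects differ widely. For child behavior, 0.64 is 64% larger than the quoted pilot value (0.64/0.390 = 1.64), so it cannot be called conservative for that outcome on the evidence the article gives.

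The subgroup sentence has a similar mismatch. A treatment comparison within one subgroup and a test of whether the effect differs between subgroups are different tests with different standard errors. The article quotes power that fits the first and plans the second.

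A reader who takes the two sentences at face value would give a null ECBI result or a null moderator result more weight as evidence of no effect than the design supports.

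**Working it through.** **Inputs from the article.** 122 per arm at 12 months; d=0.64; pilot d=0.390 for child behavior; 1:1 allocation; subgroups split 50/50, so 61 per arm in each half.

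**Assumptions not in the article.** Two-sided 5%, SD=1, an unadjusted two-group comparison, and 0.390 read as a between-group effect.

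**Formula.** Power = Φ(d/SE − 1.96), with SE = √(2/n) for n per arm.

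**1. The plan's own figures.**
- Main: SE = √(2/122) = 0.128; 0.64/0.128 = 5.00; power = Φ(3.04) = 99.9%. This agrees with >95%.
- Subgroup: SE = √(2/61) = 0.181; 0.64/0.181 = 3.53; power = Φ(1.57) = 94.2% (noncentral t: 93.9%). This reproduces the stated 95% closely, so that figure is consistent with a treatment comparison inside one half-sample.

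**2. Child behavior at its quoted pilot effect.**
- 0.390/0.128 = 3.05; power = Φ(1.09) = 86.1% (noncentral t: 85.9%).
- Effect detectable with 95% power: (1.960 + 1.645) × 0.128 = 0.46.
- For scale, 95% power at 0.390 would take 2 × (1.960 + 1.645)²/0.390² = 171 completers per arm, or 342 against the 244 planned.
- Inside one half-sample, d=0.390 gives about 58% (noncentral t: 57%).

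**3. Sensitivity of the 86%.**

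| Change of assumption | Power for child behavior |
|---|---|
| One-sided 5% | 91.9% |
| Two-sided 2.5% | about 79% |
| Baseline-adjusted, assumed r=0.5 (SE × √(1−r²)) | 94.0% |
| Baseline-adjusted, assumed r=0.7 | 98.9% |
| Unadjusted at the 3-month size (328/2 = 164 per arm) | 94.2% |
| 0.390 is pre-post, standardized by the SD of change, r=0.3: d = 0.390 × √(2(1−r)) = 0.46 | 95.0% |
| The same with r=0.7: d = 0.30 | 65.5% |

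**4. Moderator tests.** The interaction is the difference between two subgroup effects, each with variance 2/61, so SE = √(4/61) = 0.256. This is twice the 0.128 of the overall effect.
- Difference of 0.64 SD between halves: 0.64/0.256 = 2.50; power = Φ(0.54) = 70.5%.
- Difference of 0.32 SD: 0.32/0.256 = 1.25; power = Φ(−0.71) = 23.9%.
- Difference detectable with 95% power: 3.605 × 0.256 = 0.92 SD.
- An uneven split lowers this further: at 30/70, a 0.64 SD difference has 63% power.

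This calculation applies to the two-level moderators (sex and baseline intensity). It does not describe intervention step.

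**The case against.** The strongest reply is that nothing is miscalculated. The figures follow from d=0.64, and the text does not say that 0.64 applies to child behavior. Study Design puts positive parenting first and sees child behavior as mediated by it; against eta-squared 0.850, 0.64 looks cautious. The phrase about pilot data may also cover the initial pilot, whose effect sizes are not quoted. This stands as far as it goes: the arithmetic is right, and *conservatively* may be fair for parenting. But the article gives one power figure for a trial with two co-primaries, and the only child-behavior effect it quotes is well below 0.64.

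Second, 86% describes a simpler analysis than the one planned. Primary Efficacy Analysis specifies repeated measures with baseline behavior severity in the model, which could recover much of the loss. This also stands, and it makes 86% conditional. The sample-size section, however, claims no such gain and states no correlation.

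Third, the subgroup sentence claims no interaction power. That is true, but moderation is the subgroup question that the analysis section sets out, so the quoted figure does not inform it.

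A reader might be tempted to go further in three ways that the documents do not support:
- That power falls well below 86% because families who stop after the introductory step dilute the effect. The article gives no share of such families, and the 0.390 comes from the stepped-care pilot, which may already include them.
- That the pilot effects are pre-post changes within the program. The article does not say which kind they are.
- That the trial is underpowered. Even 86% exceeds the customary 80%.

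**Conclusion.** The concern holds in a limited form. The >95% claim at a conservative d=0.64 may be sound for positive parenting, but it is not supported for the child-behavior co-primary. There, the quoted pilot effect gives about 86% under the assumptions listed, and about 94% with baseline adjustment at an assumed correlation of 0.5. The exact figure cannot be fixed from the article, because the significance level and the type of the 0.390 effect are not stated.

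The 95% subgroup power is right, to within about a point, for a within-half comparison at d=0.64. It is not the power of the planned moderator tests, which is about 70% if the halves differ by a full 0.64 SD and about 24% for half that difference. The 0.64 SD interaction is itself an assumption, and a generous one.

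Severity is moderate: the power is overstated for one co-primary and for the moderator tests.

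**What to change.** In Sample Size and Power Analysis, and correspondingly in the abstract:

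1. State power separately for each co-primary: DPICS at d=0.64 (above 99% on the simple two-group calculation) and ECBI at d=0.39, giving the significance level, whether the 0.390 is pre-post or between-group, and any baseline correlation relied on.
2. Give the effect detectable with 95% power at 122 per arm (about 0.46 in the unadjusted case).
3. Apply *conservatively* to positive parenting only.
4. Say that the subgroup figure is for a treatment comparison within one half-sample at d=0.64, and add the interaction power for the planned moderator tests (about 70% for 0.64 SD and 24% for 0.32 SD).

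The cost is text only. The stated power becomes less favorable; no families are added and no analysis changes.

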### Planned Statistical Analysis

A mixed method approach will be taken with quantitative analyses conducted using SPSS Statistics (IBM Corp) [39] and qualitative analyses conducted using NVivo (Lumivero) [40].

#### Feasibility and Acceptability Analysis

Preliminary descriptive analyses will be used to assess the characteristics of families who participated in the trial, including each program step. Descriptive data will also be computed for adherence, program fidelity, costs, and maintenance. Parent reports of acceptability, adoption, and suggested adaptability of the program by families in the treatment condition, reported in the Parent Acceptability Questionnaire, will be examined qualitatively using cross-case thematic analyses [32,41]. Parent reports and the corresponding case analyses will be used to determine commonalities, differences, and inherent contextual properties that may explain these commonalities and differences across the cases [42]. The results of the case-specific analyses will be entered into a metamatrix to permit thematic analysis across cases. A final thematic table will be created to ensure a coherent, internally consistent, yet distinctive representation of the identified cross-case themes. The essence, scope, and content of the identified themes will be summarized in the final thematic table.

#### Primary Efficacy Analysis

Primary efficacy analysis will be conducted using an intent-to-treat approach. Generalized estimating equations for longitudinal count-level data having a Poisson distribution will be used to examine changes on the DPICS positive parenting composite. We will account for missing data with the Kenward-Roger degrees of freedom command and using a random intercept with the appropriate covariance structure to allow for unbalanced covariance matrices. The main effect of the program on positive parenting skills will be tested by linear contrast of adjusted DPICS mean change scores from baseline to 3 months between groups. We will also refit the regression model to include stratification variables (sex, baseline behavior intensity) and intervention step as moderators of the effect of treatment. The co–primary outcome of child behavior, as well as continuous secondary outcomes of quality of life and parent mental health, will be tested with repeated-measures analyses including condition, stratification variables (ie, sex assigned at birth and baseline child behavior severity), intervention step, and their interactions as fixed effects. Individual subjects as random effects will be adjusted to the data [43,44]. Sensitivity analyses will be carried out to replicate the analyses [29] from the initial adaptation of the I-InTERACT-North program into a stepped-care model for children with neurological risk, examining the preliminary efficacy in changes in positive parenting skills and child behavior based on intervention step. Finally, we will replicate the analyses conducted by Wade and colleagues [25] in the RCT of the original version of I-InTERACT for children with TBI, testing a moderated mediation model using regression-based process modeling to assess the indirect effects of treatment group on child behavior at 12-month follow-up through the change score for positive parenting.

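### The DPICS co-primary analysis is named as a Poisson GEE, but its missing-data sentence describes a mixed model and presents Kenward-Roger degrees of freedom as missing-data handling

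*Protocol article*

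**What the plan says.** In the protocol article, Primary Efficacy Analysis opens with the analysis principle: "Primary efficacy analysis will be conducted using an intent-to-treat approach". The DPICS model follows: "Generalized estimating equations for longitudinal count-level data having a Poisson distribution will be used to examine changes on the DPICS positive parenting composite". The abstract's Methods paragraph names the same model class: "Generalized estimating equations will be used to examine changes in positive parenting".

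The sentence directly after the DPICS model says: "We will account for missing data with the Kenward-Roger degrees of freedom command and using a random intercept with the appropriate covariance structure". It adds that this is meant to accommodate unbalanced covariance matrices. The next sentence returns to DPICS and fixes the test as a "linear contrast of adjusted DPICS mean change scores from baseline to 3 months between groups".

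Child behavior (ECBI) and the continuous secondary outcomes are described later, as repeated-measures analyses with their own random-effects sentence: "Individual subjects as random effects will be adjusted to the data".

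On expected follow-up, Sample Size and Power Analysis says of the 382 families expected to consent: "we anticipate that 328, 282, and 244 families will complete the 3-month, 6-month, and 12-month follow-up measurements, respectively". The article states no imputation, weighting or missingness assumption.

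**The concern.** The two halves of the DPICS specification belong to different model classes. A GEE models the population mean with a working correlation and sandwich errors; it has no random effects. A random intercept belongs to a mixed model. Kenward-Roger adjusts standard errors and denominator degrees of freedom in mixed models; it does not impute, weight or model a missing value.

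Two things are at stake. First, an analyst cannot follow both sentences, so the model for a co-primary outcome is not settled by the text. Second, the two models make different demands on the missing data:

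- A likelihood-fitted mixed model is valid under missing at random.
- An unweighted GEE in general needs data missing completely at random, or a working correlation close to the truth to be approximately unbiased.

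An intent-to-treat comparison with families missing at the primary time point rests on that assumption, and the article does not say which one it makes.

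**Working it through.** **1. Which analysis the missing-data sentence belongs to.** It stands between the sentence naming the Poisson GEE for DPICS and the sentence defining the DPICS contrast. The ECBI and secondary-outcome models come afterwards with their own random-effects sentence. The natural reading is that it governs DPICS.

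**2. Element by element.**

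| Element in the text | Part of a GEE? | Addresses missing outcomes? |
|---|---|---|
| Poisson GEE | Yes | Not under missing at random in general |
| Random intercept | No | Yes, under missing at random, if fitted by likelihood as a mixed model |
| Kenward-Roger | No | No |

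**3. How much is missing.** Inputs: 382 families and 86% retained per wave (Sample Size and Power Analysis).

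- Reproducing the stated completers: 382 × 0.86 = 328.5; 382 × 0.86² = 282.5; 382 × 0.86³ = 243.0. The article gives 328, 282 and 244, which agrees to within about one family.
- Missing at 3 months: 1 − 328/382 = 14.1%.
- Missing at 6 months: 1 − 282/382 = 26.2%.
- Missing at 12 months: 1 − 244/382 = 36.1%.

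The fixed DPICS contrast is at 3 months, so 14% is its figure. The 36% bears on the part of Hypothesis 2 that claims benefit at 12 months.

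**4. Does the choice of model matter? An adverse illustration.** Everything here except 382 families and about 14% dropout per wave is assumed: Poisson counts, random-intercept SD 0.6 on the log scale, true log rate ratios of 0.50 at 3 months and 0.40 at 12 months. Dropout depends on the last observed count, with low scorers leaving the treated arm and high scorers leaving care as usual. There were 100 simulated trials per scenario; Monte Carlo standard error was at most 0.009.

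| Model | Completely at random, 3 / 12 months | Adverse dropout, 3 / 12 months |
|---|---|---|
| GEE, independence | 0.500 / 0.402 | 0.593 / 0.675 |
| GEE, exchangeable | 0.500 / 0.405 | 0.499 / 0.391 |
| Random-intercept Poisson, maximum likelihood | 0.500 / 0.408 | 0.495 / 0.389 |

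The excess for the independence GEE is 0.593 − 0.50 = 0.093 at 3 months and 0.675 − 0.40 = 0.275 at 12 months.

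**5. How far this depends on the dropout pattern.** A second simulation used 3,000 families per arm, 3 replicates, about 64% retention at 12 months, random-intercept SD 0.6, dropout slope 0.7, and true values of 0.40 and 0.20 (all assumed).

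| Dropout pattern | GEE independence, 3 / 12 months |
|---|---|
| Opposite directions by arm | 0.49 / 0.48 |
| Outcome-dependent in one arm only | 0.44 / 0.33 |
| Same direction in both arms | 0.40 / 0.21 |

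The exchangeable GEE stayed at 0.39–0.40 and 0.19–0.21 throughout. Bias needs both an independence working correlation and dropout that differs by arm.

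**6. The mixed-model branch.** If within-family counts have variance φ times their mean and model-based Poisson errors are used, the true type I error of a nominal two-sided 5% test is 2 × (1 − Φ(1.96/√φ)):

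- φ = 1.5: 1.96/1.225 = 1.600, giving 11%.
- φ = 2: 1.96/1.414 = 1.386, giving 17%.
- φ = 3: 1.96/1.732 = 1.132, giving 26%.

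Simulation with 164 families per arm (328/2) and 2,000 replicates gave 10%, 17% and 25%. The article gives no DPICS dispersion, so this range of φ is an assumption.

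**The case against.** The strongest defence is that this is loose labelling. Apart from the name GEE, the sentence describes a random-intercept Poisson mixed model, and Kenward-Roger-type degrees of freedom exist for some pseudo-likelihood fits of such models. An article may also leave the working correlation, variance estimator, overdispersion and imputation model to an analysis plan, which is not shown here.

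Much of this stands, and it limits what may be concluded. Four stronger readings are tempting and not supported:

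- *The stated method does nothing about missing data.* Too strong. A random intercept fitted by likelihood to all observed visits is valid under missing at random. Only the Kenward-Roger half fails as missing-data handling.
- *The primary contrast faces 36% missing data.* The fixed DPICS contrast is at 3 months, where the article's figures give 14%.
- *The DPICS result will be biased, or its false-positive rate will be several times 5%.* The documents give neither a dropout mechanism nor a DPICS dispersion. The bias figures need an independence working correlation, from which the reference to an appropriate covariance structure points away. The error rates need overdispersion together with model-based errors.
- *The model will be chosen after the data are seen.* Not established. Follow-up runs to January 2029, so an analysis plan could still settle it beforehand.

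The defence does not remove the core. The article is not silent: it names a GEE twice, attaches a mixed-model device to it, and calls a degrees-of-freedom correction missing-data handling. That is an error in what is stated, not a detail deferred.

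**Conclusion.** The concern holds as a contradiction in the specification. The DPICS co-primary analysis mixes a marginal and a mixed model, and Kenward-Roger is mislabelled as a way of accounting for missing data. This conclusion follows from the text and needs no simulation.

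The consequence is conditional. Expected missingness is 14% at the DPICS contrast and 36% at 12 months, enough for the missing-data assumption to matter. Under assumed arm-differential dropout, the independence GEE was biased upward, by less at 3 months than at 12, while the exchangeable GEE and the likelihood mixed model stayed near the truth. Under dropout completely at random, all three agreed. The 11% to 26% type I error is likewise a worst-case illustration, for an assumed variance-to-mean ratio of 1.5 to 3 with model-based errors. No sample-size or power figure is affected.

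**What to change.** Name one DPICS model, with its variance estimator and missingness assumption, before analysis. Either of these is coherent:

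- **(a) Mixed model.** A random-intercept count model (Poisson or negative binomial, log link) with condition, visit and condition × visit, fitted by maximum likelihood to all observed visits under a stated missing-at-random assumption, with errors robust to overdispersion.
- **(b) Marginal model.** A Poisson GEE with sandwich errors and a non-independence working correlation, combined with multiple imputation or inverse-probability weighting.

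In both cases the 3-month test is the condition × visit contrast for that visit. Choosing between (a) and (b), or between Poisson and negative binomial, is for the trial team.

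Under either option, remove Kenward-Roger as the missing-data method for DPICS. It may stay as the degrees-of-freedom method for the linear ECBI mixed model.

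The cost is a change of wording and modest extra programming. No additional families or measurements are needed. The article reports 24 families enrolled by September 2024 and recruitment through January 2028, so the change can be made well before analysis.

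### The primary DPICS analysis credits Kenward-Roger and a random intercept with handling missing data inside a GEE; neither fits, so the model and its dropout assumption are left undetermined

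*Protocol article*

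**What the plan says.** Under Primary Efficacy Analysis, the Protocol article gives the DPICS model: "Generalized estimating equations for longitudinal count-level data having a Poisson distribution will be used to examine changes on the DPICS positive parenting composite". The Methods part of the Abstract names the same method. The next sentence of that section gives the missing-data rule: "We will account for missing data with the Kenward-Roger degrees of freedom command and using a random intercept with the appropriate covariance structure". It adds that this lets the covariance matrices be unbalanced.

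The section opens with the principle that "Primary efficacy analysis will be conducted using an intent-to-treat approach". The treatment effect on DPICS is to be "tested by linear contrast of adjusted DPICS mean change scores from baseline to 3 months between groups". Hypothesis 2 (Study Design) goes further in time: the treated families should also "remain improved compared with CAU at 12 months".

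Under Sample Size and Power Analysis the plan forecasts its own losses from 382 enrolled: "we anticipate that 328, 282, and 244 families will complete the 3-month, 6-month, and 12-month follow-up measurements".

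The analyses labelled as sensitivity analyses concern something else: "Sensitivity analyses will be carried out to replicate the analyses [29] from the initial adaptation of the I-InTERACT-North program".

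**The concern.** The sentence assigns a job to a tool that cannot do it. Kenward-Roger adjusts the estimated covariance of the fixed effects and the denominator degrees of freedom in a linear mixed model fitted to a small sample. It recovers no missing outcome, removes no attrition bias and does not alter the assumption about why outcomes are missing. It is not part of a GEE.

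The random intercept raises a second difficulty. A GEE models the marginal mean with a working correlation and has no random effects, so the sentence describes a mixed model while the sentence before it describes a GEE. The two families treat dropout differently:

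- **Unweighted GEE:** in general consistent only if dropout is completely random or depends only on covariates in the model.
- **Likelihood-based Poisson mixed model:** if correctly specified, valid when dropout depends on observed data (missing at random). That property comes from the likelihood, not from Kenward-Roger.

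At stake is the first co-primary outcome. If dropout is related to earlier parenting skill and the relation differs by arm, the first model can turn it into an apparent treatment effect, while the second is largely protected. As written, a reader cannot tell which applies.

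**Working it through.** **1. The plan's loss figures.** Inputs from Sample Size and Power Analysis: 382 enrolled and an 86% adherence rate, applied once per follow-up interval.

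- 382 × 0.86 = 328.5 (stated 328)
- 382 × 0.86² = 282.5 (stated 282)
- 382 × 0.86³ = 243.0 (stated 244)

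The stated figures are reproduced to within about one family. Cumulative loss:

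- 3 months: (382 − 328)/382 = 54/382 = 14.1%
- 6 months: (382 − 282)/382 = 100/382 = 26.2%
- 12 months: (382 − 244)/382 = 138/382 = 36.1%

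The specified DPICS contrast is at 3 months, so 14% applies to it. The 36% applies to the sustained benefit in Hypothesis 2.

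**2. Does the choice of model matter at these losses?** The documents give no DPICS distribution and no dropout by arm, so every parameter here is an assumption except the 14% loss per interval. Four visits of Poisson counts were simulated with baseline mean exp(log 8 + b), where b is a normal random intercept with SD 0.6. The true rate ratio was 1.5 at every follow-up, with 4 runs of 8,000 families. Where dropout was not completely random, its log-odds changed by 1.2 (odds × e^1.2 = 3.3) per 0.7 units of the log of the last observed count. Lower counts left more often in both arms (same direction), or lower counts left in the treated arm and higher counts in the control arm (opposite direction).

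Estimated rate ratios at 3 / 6 / 12 months, true value 1.5:

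| Dropout | GEE, independence | GEE, exchangeable | Random-intercept likelihood |
|---|---|---|---|
| Completely random | 1.49 / 1.49 / 1.52 | 1.49 / 1.50 / 1.51 | 1.49 / 1.50 / 1.51 |
| Same direction in both arms | 1.50 / 1.52 / 1.50 | 1.52 / 1.55 / 1.54 | 1.51 / 1.52 / 1.50 |
| Opposite direction by arm | 1.76 / 2.03 / 2.29 | 1.52 / 1.54 / 1.54 | 1.51 / 1.52 / 1.52 |

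In the last row the independence GEE is too high by 1.76/1.5 − 1 = 17% at 3 months and 2.29/1.5 − 1 = 53% at 12 months. The other two models are within about 3%. The likelihood model has the advantage of matching the way the data were generated.

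**3. A milder pattern.** A separate simulation used no true effect, 382 families, overdispersed counts with mean 10, visit correlations of 0.65 (0 to 3 months) and 0.49 (0 to 12 months), and 250 to 300 replicates. Dropout odds rose 2.2-fold per SD lower last DPICS in the treated arm only. The independence GEE gave a rate ratio of 1.03 with 7% type I error at 3 months, and 1.09 with 18% at 12 months. With 250 replicates the Monte Carlo standard error of 7% is √(0.07 × 0.93/250) = 1.6 points, so the 3-month figure is barely distinguishable from 5%. Across all the scenarios run, type I error was 2% to 7% with an exchangeable working correlation and 2% to 6% with inverse-probability weights.

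**The case against.** The strongest defence is that the sentence names a random intercept as well as Kenward-Roger. If a likelihood-based Poisson mixed model is what the authors intend, the estimate is valid under missing at random, and the error is one of attribution and labelling. This stands. A reader might infer that the primary analysis is valid only under completely random dropout. The text does not support that without qualification, because it holds for only one of the two models described.

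Three further readings go too far:

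- **That the result will be badly biased.** The large figures need an independence working correlation and dropout that runs differently by arm. The plan names no working correlation and promises an appropriate covariance structure. It gives one pooled 86% rate with no split by arm. Both arms receive a gift card at each timepoint (Ethical Considerations), and control families are offered the programme after their 12-month measures (Study Design), which encourages them to stay. Arm-specific dropout is plausible, since contact with the study differs by arm, but it is an inference.
- **That the effect at 12 months would be only 64% of the estimate.** That figure is 244/382 = 0.64. It follows from assuming treated dropouts do no better than controls, and would apply equally to an imputed or weighted analysis that assumes missing at random.
- **That only completers are compared.** Both model families use every available visit, including the early visits of families who later leave.

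Nor is the absence of a missing-data sensitivity analysis an error in itself, since an article may leave that detail to an analysis plan not shown here. The misattribution is different: the article states a method, and the stated method does not do what is claimed.

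**Conclusion.** The point holds in a limited form. The Protocol article states a missing-data method for DPICS that does not address missing data, and attaches a random intercept to a model that has none. The missing-data assumption behind the first co-primary outcome is therefore undetermined: completely random or covariate-dependent dropout under the unweighted GEE, missing at random under a likelihood mixed model.

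The expected loss is 14% at the primary contrast and 36% at 12 months, from the plan's own figures. How much bias follows cannot be read from the documents. Under the assumed mechanisms it ranged from negligible to material, and was material only for an independence GEE with dropout differing by arm. The point rests on the definitions of the methods and does not depend on the simulated sizes. It should be fixed. It does not show that the trial's result will be wrong.

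**What to change.** Delete the claim that Kenward-Roger accounts for missing data, and name one model for DPICS with its assumption:

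- **(a)** a likelihood-based count mixed model using all visits, stated to be valid under missing at random; or
- **(b)** the GEE with a named working correlation, either after multiple imputation by arm or weighted by the inverse probability of remaining under observation. Imputation or weights would use baseline and earlier DPICS, ECBI and DASS and the stratification variables.

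Keep Kenward-Roger only for the Gaussian mixed models of continuous outcomes. Preferably add one reference-based or delta-shifted sensitivity analysis for the co-primary outcomes, kept separate from the replication of the pilot analyses.

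Table 1 shows that DPICS, ECBI and DASS are collected at every timepoint, so no new data are needed. The cost is revised wording, some extra programming and possibly slightly wider intervals. With 24 families enrolled by September 2024 and follow-up planned to January 2029 (Results), the change can be made well before analysis.
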